**Fig. 1 Fig1:**
[figure not shown]
Recruitment plan

### Experimental and control interventions

Following randomisation, oral intake of PETN or placebo two times daily will be continued until 36^6^ weeks. Maternal and fetal status and condition will be assessed every 4 weeks during the treatment period and at 38^6^ to 40^0^ weeks. (Table 1) Outcome data will be collected after delivery for neonatal (weight, height, APGAR 1′/5′/10′, umbilical artery pH, gestational age at birth, admission to the neonatal intensive care unit, respiratory distress syndrome grade III or IV, occurrence of intraventricular haemorrhage grade III or IV or parenchymal bleeding or periventricular leukomalacia, necrotized enterocolitis, neonatal death) and maternal pregnancy associated morbidity. Additionally, data on child development will be documented on growth, health status and intellectual development at the age of 12 months, by collecting the routine check-up data from the paediatricians. (Table 1).

**Table 1 Tab1:** Study procedures

Study Period	Recruitment period	Treatment period (12–19 weeks) Study visits fourweekly				Post-Treatment-Follow-up		
Treatment	start at inclusion	oral intake of 50 mg PETN/Placebo 2 times daily				Follow up		Follow up child
Event/Visit	Inclusion visit at 19^0^ to 22^6^ weeks	24^0^ to 24^6^ weeks	28^0^ to 28^6^ weeks	32^0^ to 32^6^ weeks	36^0^ to 36^6^ weeks	38^0^ to 40^0^ weeks	after delivery^h^ (no visit)	Routine check-up at the age of 12 month^i^
Informed Consent	x							
Inclusion/Exclusion Criteria	x							
Randomisation	x							
Ultrasound ^a^	x	x	x	x	x	x		
Maternal status^b^	x	x	x	x	x	x	x (at admission for delivery)	
Haematology/Urinanalysis^c^	x	(x)	x	(x)	x	x	x (if available)	
Maternal condition^d^	x	x	x	x	x	x		
Concomitant medication^e^	x	x	x	x	x	x		
Checking for AEs incl. SAEs		x	x	x	x	x	x	x
Perinatal outcome^f^							x	
Maternal morbidity^g^							x	
Data on child growth and development								x

^a^assessment of fetal growth: head and abdomen circumference, femur length, doppler of aa. aterinae, a. umbilical and a. cerebri media, amniotic fluid index

^b^assessment of maternal status: blood pressure, weight

^c^assessment of haematology and urine: blood count, ASAT, ALAT, LDH, proteinuria and determination of sflt and PlGF amounts and ratio where possible

^d^assessment of maternal condition: head ache, nausea/vomiting, ear or eye symptoms, pain in the upper abdomen, oedema, others

^e^concomitant medication: name, dosage, frequency, duration, reason of intake

^f^assessment of perinatal outcome: weight, height, growth centile, APGAR 1`/5`/10`, pH of umbilical artery, exact gestational age, admission to neonatal intensive care unit, respiratory distress syndrome, occurrence of intraventricular haemorrhage, necrotized enterocolitis, neonatal death

^g^assessment of maternal morbidity: e. g. Preeclampsia, HELLP syndrome, abruption placentae

^h^no visit required, post-delivery data will be collected as copies of health reports, discharge or pregnancy reports

^i^Follow up of the children will be collected as copies of the mandatory standard care visit at the pediatrician at the age of 1 year

### Assessment of safety

Monitoring of selected safety data (maternal serum and clinical parameters, fetal growth control and control of utero-placental and fetal perfusion) is scheduled every 4 weeks. Monitoring of Adverse Events (AEs) and Serious Adverse Events (SAEs) is established. A data safety monitoring board is constituted to supervise safety events and outcome data of the neonates born during the ongoing study. The data safety monitoring board has met on a regular basis; three times so far, did not find any peculiarities and had no recommendations on protocol changes.

### Statistical analysis

Baseline characteristics of patients will be compared by descriptive statistics to assess the success of randomization. The primary endpoint (binary variable) will be presented by group-specific incidences. The confirmatory test of the treatment effect stratified for risk-groups will be performed by the Mantel-Haenszel test. Mantel-Haenszel estimates of relative risks and their 95% confidence intervals will be calculated. Primarily, data will be analyzed according to the intent-to-treat (ITT) principle. The ITT-population will include all randomized patients with valid primary outcome data who have received at least one dose of study medication (full analysis data set). The drop-out rate is expected to be 10%. Missing values of the primary endpoint are multiply imputed to confirm the robustness of the main results (sensitivity analysis). All secondary endpoints (binary variables) will be analysed by Mantel-Haenszel methods as described above. In a sensitivity analysis generalized mixed linear models with treatment and risk indicator as fixed, and centre as random factor, will be fitted to adjust for variability between study centres. Explorative analyses of endpoints will be additionally performed for subgroups according to time of delivery and maternal age. AEs/SAEs will be listed. Incidence of events and descriptive statistics (quartiles, mean, standard deviation) of laboratory safety data will be displayed in treatment groups. No adjustment for endpoint multiplicity is planned. All tests will be done at a comparison-wise significance level of 0.05.

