### Primary outcome measures

As primary efficacy endpoint development of FGR (< birth weight below the 10th centile) or perinatal death as a composite outcome was proposed in accordance to the pilot study [12]. Key secondary endpoints are severe morbidity and mortality as composite of severe FGR, intrauterine or neonatal death or placental abruption, birth weight below the 3rd, 5th and 10th centile according to Voigt [15], development of FGR requiring delivery before 30 and before 34 weeks` gestation, spontaneous preterm delivery before 34 weeks and before 37 weeks gestation, rate of neonatal intensive care unit admission and neonatal complications like the need of ventilation, occurrence of intraventricular hemorrhage II – IV ° or necrotized enterocolitis.

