### Proposed sample size/power calculations

Sample size calculation is based on results generated from our pilot trial [12]. Since additional risk factors increase the risk of FGR a stratified randomisation and analysis is planned for two strata. A 2:1 ratio was observed for low and high risk patients in the trial. Proportion of FGR or perinatal death was 0.42 in the low-risk and 0.69 in the high-risk stratum of the placebo group. We discovered an odds ratio of 0.41 (PETN vs. placebo) in the pilot trial. More conservatively, we want to be able to find a 50% risk reduction (i.e. an odds ratio of 0.5) in the here proposed study, which would still be of profound clinical relevance. Accordingly, we will need a sample size of 290 patients to detect this treatment effect by a Mantel-Haenszel test with a power of 80% at a two-sided alpha-level of 0.05 (nQuery 7.0). Assuming a dropout rate of about 10% a total of 324 patients should be randomized.

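### Fetal biometry is scheduled at inclusion, but no stated analysis of the birth-weight-centile endpoint uses it: a cheap gain in precision left unused, not an error

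*Protocol article*

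**What the plan says.** The Primary outcome measures section defines the endpoint: "As primary efficacy endpoint development of FGR (< birth weight below the 10th centile) or perinatal death as a composite outcome".

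In the section Experimental and control interventions, Table 1 marks ultrasound at the inclusion visit (19+0 to 22+6 weeks) and at every later visit. Footnote a describes its content, beginning: "assessment of fetal growth: head and abdomen circumference, femur length".

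The Statistical analysis section names the confirmatory test: "The confirmatory test of the treatment effect stratified for risk-groups will be performed by the Mantel-Haenszel test". Mantel-Haenszel relative risks with 95% confidence intervals go with it. A sensitivity analysis uses "generalized mixed linear models with treatment and risk indicator as fixed, and centre as random factor". Fetal size at inclusion appears in neither.

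**The concern.** The endpoint splits size for gestational age at birth at the 10th centile and adds perinatal death. The inclusion ultrasound measures the same trait, fetal size, before the first dose. The Exclusion criteria do not rule out a fetus that is already small, so size at entry is free to vary. If it predicts the endpoint, part of the variation in outcome is settled before treatment starts, and an analysis that ignores it treats that part as noise.

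What is at stake is efficiency: the trial is planned at 80% power, and the data that might raise this are already scheduled. Type I error is not at stake. The omission is also a stated choice and not a gap left by condensing the protocol, because the article names the confirmatory test, its single stratifier and the terms of the sensitivity model.

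**Working it through.** **Inputs from Proposed sample size/power calculations.** "Proportion of FGR or perinatal death was 0.42 in the low-risk and 0.69 in the high-risk stratum of the placebo group". "A 2:1 ratio was observed for low and high risk patients in the trial". The effect is given as "i.e. an odds ratio of 0.5", and the test is planned "with a power of 80% at a two-sided alpha-level of 0.05". The evaluable sample is 290. The allocation ratio is not stated; 1:1 is assumed.

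**Step 1: reproduce the plan's figure.** With odds ratio 0.5, the PETN rate is q = 0.5p / (1 − p + 0.5p).
- Low risk: 0.21 / 0.79 = 0.266.
- High risk: 0.345 / 0.655 = 0.527.
- Overall: 51.0% on placebo and 35.3% on PETN.

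With stratum shares s = 2/3 and 1/3 and p̄ = (p + q)/2:
- D = Σ (s/4)(p − q) = 0.03930
- V0 = Σ (s/4) p̄(1 − p̄) = 0.05741
- V1 = Σ (s/4) [p(1 − p) + q(1 − q)]/2 = 0.05586
- N = [(1.960√V0 + 0.842√V1) / D]² = 289.3, so 290. Power at 290 is 80.1%.

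The plan's sample size is reproduced.

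**Step 2: add fetal size at inclusion.** No correlation is given in the documents, so rho is an assumption. Within each stratum, a latent growth score is rho·z + √(1 − rho²)·e, where z is the fetal-size z-score at inclusion and e is independent standard normal noise. The event occurs when the score falls below the normal quantile of the event rate for that arm and stratum. R² is the share of the variance of the binary endpoint explained by z, pooled over arms and strata.
- Equivalent sample size: 290(1 − R²).
- Adjusted power: Φ[(1.960 + 0.842)/√(1 − R²) − 1.960], which starts from exactly 80%.
- Fall in standard error: 1 − √(1 − R²).

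| Assumed rho | R² | Adjusted power at 290 | N for the same power | Fall in standard error |
|---|---|---|---|---|
| 0.1 | 0.006 | 80.2% | 288 | 0.3% |
| 0.2 | 0.024 | 81.0% | 283 | 1.2% |
| 0.3 | 0.054 | 82.2% | 274 | 2.8% |
| 0.4 | 0.098 | 83.9% | 262 | 5.0% |
| 0.5 | 0.154 | 86.1% | 245 | 8.0% |

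**Step 3: check by simulation.** There were 193 low-risk and 97 high-risk women per trial, with 8,000 trials per rho. The Mantel-Haenszel test is compared with the likelihood-ratio test from a logistic model on treatment, risk group and z.

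| Assumed rho | Mantel-Haenszel | Adjusted | Difference |
|---|---|---|---|
| 0 | 79.3% | 79.9% | 0.6 |
| 0.2 | 80.8% | 82.0% | 1.2 |
| 0.3 | 79.6% | 81.7% | 2.1 |
| 0.4 | 80.3% | 84.3% | 4.0 |
| 0.5 | 80.2% | 86.9% | 6.7 |

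Under the null (4,000 trials per rho) the adjusted tests rejected in 5.1% to 5.5% of trials. A second, smaller simulation (3,000 trials per rho, Monte Carlo error about 0.7 points) gave 79.0% against 79.7% at rho 0.2, 80.7% against 82.8% at 0.3, 80.9% against 83.4% at 0.4, and 79.1% against 86.6% at 0.5. It shows the same pattern within its error.

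**The case against.** The strongest case against is that nothing here is wrong. A risk-stratified Mantel-Haenszel test matches the stratified randomisation, the sample-size method and the relative-risk scale of the report. It already adjusts for a strong predictor (placebo rates 0.42 and 0.69). This stands: the planned test is sound, and a protocol need not justify every covariate that it omits.

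The size of the gain rests on an unsourced rho. The trial targets growth failure that develops after entry, so size at mid-gestation may predict it only weakly. This also stands, and is why the range has to be shown from zero.

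The simulation is somewhat kind to adjustment. It puts perinatal death on the same latent size scale and gives the covariate its correct form. Even at rho 0 the adjusted test shows 0.6 points more, so about half of the 1.2-point gain at rho 0.2 may not come from the covariate. The calculation in Step 2 does not have that offset and gives about 1 point there.

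A reader might infer that the trial is underpowered, or that a chance imbalance in fetal size would bias the result. The documents support neither. The test delivers its stated 80%, and random imbalance is already allowed for in the test's error rate and the confidence interval.

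A reader might also call the gain free. It is cheap, but a reference and a scoring rule must be chosen, and the confirmatory test would change after enrolment began in August 2017.

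Finally, the analysis plan is not shown and may hold further supportive models. That limits the claim to the analyses stated in the article, but the confirmatory test is among them.

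**Conclusion.** The point holds as a missed efficiency of low priority. Fetal size is scheduled to be measured before treatment, it is closely related to what the endpoint measures, and no analysis stated in the article uses it. Under the latent-normal model with 1:1 allocation, adjusting adds about 0 to 2 points of power at 290 women for rho up to 0.3, about 4 at 0.4 and about 6 to 7 at 0.5. Nothing is lost at rho 0, and type I error stays near 5%. A gain above 5 points is seen only at rho 0.5, the top of the assumed range, and nothing in the documents supports that value over a lower one.

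**What to change.** Before unblinding:
- Prespecify one gestational-age-specific fetal-size z-score at inclusion. Name the biometry reference and the rule for combining the three measurements. Inclusion spans four weeks of gestation, so raw measurements will not serve; the dating described under Determination of primary and secondary measures makes the z-score derivable.
- Add it to risk group in the primary analysis, for example in a logistic model with treatment, risk group and the z-score. Report the standardised (marginal) relative risk with its 95% confidence interval, which keeps the planned scale and avoids moving to a conditional odds ratio.
- Replace a missing inclusion value by the mean pooled over both arms, so that no woman is dropped.
- Keep the risk-stratified Mantel-Haenszel test as the supportive analysis.

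**Cost:** analysis-plan wording and one derived variable, with no extra patients, visits or procedures. The primary test becomes model-based and the z-score has to be specified. Changing the confirmatory test after enrolment has begun is acceptable only if it is fixed while the trial is still blinded. If the correlation is weak, the return is small.

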**Method:**

The trial has been initiated in 14 centres in Germany. Inclusion criteria are abnormal uterine artery Doppler, defined by mean PI > 1.6, at 19^0^ to 22^6^ weeks of gestation in singleton pregnancies. Included patients will be monitored in 4-week intervals. Primary outcome measures are development of FGR (birth weight < 10th percentile), severe FGR (birth weight < 3rd centile) and perinatal death. Placental abruption, birth weight below the 3rd, 5th and 10th centile, development of FGR requiring delivery before 34 weeks` gestation, neonatal intensive care unit admission, and spontaneous preterm delivery < 34 weeks` and 37 weeks` gestation will be assessed as secondary endpoints. Patient enrolment was started in August 2017. Results are expected in 2020.

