### Methods against bias

Patients will be randomly assigned to treatment groups in blocks of varying size. Randomization will be stratified by center and by an indicator for low or high risk of FGR. Patients will be classified as high risk in case of pre-existing hypertension, pre-existing diabetes or obstetric history of FGR, late pregnancy loss, stillbirth, abruption placentae, preterm delivery, preeclampsia or HELLP-syndrome. All others are at low risk. PETN and placebo will be administered in a double-blind fashion. Primary analysis will be performed in the intent-to-treat population.

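### Randomisation is stratified by centre and risk, but the confirmatory test is stratified by risk only, so it is conservative and loses some power if event rates differ between centres

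*Protocol article*

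**What the plan says.** Under Methods against bias, the article states: "Randomization will be stratified by center and by an indicator for low or high risk of FGR". Blocks are of varying size. The Abstract (Method) gives the number of sites: "The trial has been initiated in 14 centres in Germany". Two risk groups in 14 centres make 28 randomisation strata.

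Under Statistical analysis, the primary test uses one of the two factors: "The confirmatory test of the treatment effect stratified for risk-groups will be performed by the Mantel-Haenszel test". Mantel-Haenszel relative risks with 95% confidence intervals accompany it. The sample-size section agrees: "a stratified randomisation and analysis is planned for two strata". Centre enters in one place: "In a sensitivity analysis generalized mixed linear models with treatment and risk indicator as fixed, and centre as random factor, will be fitted", with the stated purpose of adjusting for variability between centres. The article gives no reason for leaving centre out of the confirmatory test.

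**The concern.** Stratified blocking tends to balance the two arms within each centre and risk group. If some centres have higher rates of growth restriction or perinatal death than others, most of that between-centre variation cancels from the treatment comparison. A Mantel-Haenszel variance computed within risk groups only still counts it as noise. The standard error is then too large, the p-value tends to be too large and the interval for the relative risk too wide.

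At stake is precision that the randomisation already provides and that the only confirmatory test would not use. The article itself expects centres to vary, since it plans a model to adjust for this. Recruitment through affiliated outpatient facilities (Recruitment section) makes differences in referral mix plausible.

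**Working it through.** **Step 1: reproduce the planned sample size, to see which test it belongs to.**

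Inputs from the sample-size section: "A 2:1 ratio was observed for low and high risk patients in the trial", giving weights *w* of 2/3 and 1/3; "Proportion of FGR or perinatal death was 0.42 in the low-risk and 0.69 in the high-risk stratum of the placebo group"; odds ratio 0.5; 80% power; two-sided alpha 0.05. Allocation is taken as 1:1, because the article states no ratio.

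PETN rates follow from *q* = 0.5*o*/(1 + 0.5*o*), where *o* = *p*/(1 − *p*):
- low risk: *o* = 0.42/0.58 = 0.724, so *q* = 0.362/1.362 = 0.266
- high risk: *o* = 0.69/0.31 = 2.226, so *q* = 1.113/2.113 = 0.527

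Two-stratum Mantel-Haenszel formula without continuity correction, where *p̄* is the mean of *p* and *q* in a stratum:
- D = ¼ Σ*w*(*p* − *q*) = ¼(0.1028 + 0.0544) = 0.0393
- V0 = ¼ Σ*w p̄*(1 − *p̄*) = ¼(0.1502 + 0.0794) = 0.0574
- V1 = ⅛ Σ*w*[*p*(1 − *p*) + *q*(1 − *q*)] = ⅛(0.2925 + 0.1544) = 0.0559
- N = (1.960√V0 + 0.842√V1)²/D² = 289.3, hence 290

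Power at 290 is 80.1%. For dropout, 290/0.9 = 322.2, so 323 against the stated 324, a rounding difference. The plan's figure is reproduced, and it belongs to a test stratified by risk only.

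**Step 2: compare the two analyses by simulation.**

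Settings: N = 290; 14 centres of unequal size; permuted blocks of 4 or 6 within centre and risk group (assumed, since the article says only that block size varies); placebo rates averaged over centres held at 0.42 and 0.69; odds ratio 0.5 within centre; normal centre effects on the logit scale; 8,000 trials per cell. The between-centre SD is an assumption, so a range is shown.

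| SD | Type I error, risk only | Type I error, centre × risk | Power, risk only | Power, centre × risk | Power lost by omitting centre |
|---|---|---|---|---|---|
| 0 | 5.0% | 5.0% | 79.9% | 79.2% | about −1 |
| 0.3 | 5.0% | 5.2% | 78.8% | 78.9% | about 0 |
| 0.5 | 4.3% | 4.7% | 76.5% | 77.3% | about 1 |
| 0.8 | 4.2% | 5.2% | 71.1% | 74.5% | about 3 |
| 1.0 | 3.7% | 5.1% | 66.6% | 71.5% | about 5 |

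Monte Carlo standard error is about 0.25 points for type I error and 0.5 points for power.

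A separate simulation with 6,000 trials per cell agrees. At SD 0.5, 0.8 and 1.0, type I error (risk only vs centre × risk) is 4.8% vs 5.3%, 3.9% vs 4.9% and 3.3% vs 4.9%. Power is 76.9% vs 77.4%, 72.0% vs 74.9% and 67.5% vs 72.4%. There is no meaningful difference at SD 0.3 or less.

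Only the gap between the two power columns measures the choice of analysis. Both columns fall as the SD rises, because an odds ratio of 0.5 within centres is a weaker effect once averaged over unlike centres.

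**Step 3: what the assumed SDs mean.**

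Take a typical centre with a low-risk placebo rate of 0.42, whose logit is −0.323. The 95% range over centres is the inverse logit of −0.323 ± 1.96 × SD:
- SD 0.3: 29% to 57%
- SD 0.5: 21% to 66%
- SD 0.8: 13% to 78%
- SD 1.0: 9% to 84%

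**Step 4: stratum sizes under the alternative.**

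290/28 gives about 10 women per stratum. At 2:1, that is about 290 × (2/3)/14 = 14 low-risk and 290 × (1/3)/14 = 7 high-risk women per centre.

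**The case against.** The strongest defence is that two strata are a coherent, prespecified choice. Test, strata and sample size agree with each other, and 290 is reproduced for exactly that test. Type I error stays at or below 5% apart from simulation error, so the choice cannot make a false positive more likely. Centre is not forgotten, since a mixed model is planned for it. The loss is clear only at SDs of 0.8 or more, which imply very wide differences between centres. Such differences look extreme for women who all meet one Doppler threshold, are already split by risk, and are assessed mainly on birth weight against one national standard. Full stratification also leaves small cells, some with one arm only, which contribute nothing to the test.

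Most of this stands, and it limits the point to a conditional loss of efficiency. It does not remove the point. The sensitivity model leaves the confirmatory p-value unchanged, and small cells can be handled by pooling.

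A reader might also infer that the sensitivity model yields a conditional odds ratio that cannot be set beside the primary relative risk. The article states neither a link function nor an effect measure for that model, and both may be settled in the full protocol or analysis plan. Nor is it a fault that baseline pulsatility index is not adjusted for: any gain would rest on an assumed prognostic strength that the article does not give.

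**Conclusion.** The mismatch is real: the only confirmatory test omits a factor used in randomisation, and no reason is given. The consequence is conditional. If centres differ, the test is conservative and loses about 1 point of power at a logit-scale SD of 0.5, 3 points at 0.8 and 5 points at 1.0. At 0.3 or less the loss is negligible. These figures rest on the assumed SD, normal centre effects, 1:1 allocation and the assumed block and centre sizes. The effect on the relative-risk interval follows from the same reasoning but was not simulated.

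Two stronger readings should be resisted. One is that the primary p-value and interval are simply wrong. They are valid on the conservative side, and only to the extent that centres differ, on which the article gives no figure. The other is that the trial is undersized. The 290 is correct for the test as planned, and the fall in absolute power in the table comes mainly from assumed centre variation that affects both analyses. This is an inexpensive improvement and not a threat to the trial's conclusions.

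**What to change.** Before unblinding, define the primary Mantel-Haenszel test and the Mantel-Haenszel relative risk as stratified by centre and risk group. Fix in advance the rule for pooling centres that recruit few women. Keep the risk-only test as a sensitivity analysis, which preserves the link to the sample-size calculation.

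This changes the wording of the analysis only. It needs no new data and no larger sample. The price is at most about 1 point of power if centres do not differ at all (79.2% against 79.9% with all 28 strata). Pooling small centres should reduce that cost, though this was not simulated.

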### Inclusion criteria

Eligible patients for the proposed trial are pregnant women recognized to be at risk of adverse pregnancy outcome associated with FGR at mid gestation. Since poor placental function and mal-perfusion of the placenta is recognized to cause FGR [3] impaired placental flow measurement is strongly associated with the development of FGR. A mean pulsatility index >95th percentile according to Cnossen et al. predicts FGR with a sensitivity of 18% with a specificity of 95% in a general population and a sensitivity of 58% for any FGR in a high risk population with a specificity of 75% [4]. The risk to develop FGR is in general higher in women with a medical history of chronic hypertension, diabetes mellitus type 2, systemic lupus erythematodes or antiphopholipid antibody syndrome and in those with prior history of adverse pregnancy outcome associated with FGR (late pregnancy loss, stillbirth, abruption placentae, preterm delivery, preeclampsia or HELLP-syndrome) [13]. Accordingly, at least one third of the pregnant women diagnosed with impaired perfusion of the uterine arteries at mid gestation will develop FGR and associated adverse pregnancy outcomes. In the presence of additional risk factors this likelihood will rise considerably.

Consequently, the Inclusion criteria are impaired uterine artery Doppler ultrasound, defined by a mean Pulsatility Index (PI) greater than 1.6 (> 95th centile of German reference population, PIA Fetal Database, Version 4.00 and higher, Viewpoint, Germany; [14]), singleton pregnancy at 19^0^ to 22^6^ weeks of gestation who are over 18 years old and provide informed consent.

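### The confirmatory test is valid and delivers its planned 80% power, but it leaves out baseline uterine artery PI; adjusting for it would be a cheap, optional gain of about 1 to 2 power points

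*Protocol article*

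**What the plan says.** **Confirmatory test.** In the Statistical analysis section: "The confirmatory test of the treatment effect stratified for risk-groups will be performed by the Mantel-Haenszel test". Mantel-Haenszel relative risks with 95% confidence intervals accompany it.

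**Sensitivity model.** The same section says that "generalized mixed linear models with treatment and risk indicator as fixed, and centre as random factor, will be fitted". Its stated purpose is to allow for differences between centres.

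**Risk indicator.** Under Methods against bias: "Patients will be classified as high risk in case of pre-existing hypertension, pre-existing diabetes or obstetric history of FGR", followed by further items of obstetric history. PI is not part of it. Randomisation is stratified by centre and this indicator.

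**Baseline PI.** Under Inclusion criteria, impaired Doppler is "defined by a mean Pulsatility Index (PI) greater than 1.6". Table 1 schedules ultrasound at the inclusion visit, and its footnote a lists "doppler of aa. aterinae, a. umbilical and a. cerebri media". A pre-treatment PI should therefore exist for every randomised woman.

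**PI as a marker of risk.** Inclusion criteria says that "impaired placental flow measurement is strongly associated with the development of FGR". It reports that a PI above the 95th percentile "predicts FGR with a sensitivity of 18% with a specificity of 95% in a general population", and gives "a sensitivity of 58% for any FGR in a high risk population with a specificity of 75" (per cent).

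**The concern.** The protocol stratifies the analysis by history because additional risk factors raise the risk of FGR. The same reasoning applies to the severity of the Doppler finding, which is the measurement that defines the trial population. PI nevertheless serves only as a yes/no entry threshold, and its continuous value appears in no stated analysis.

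Two things are at stake. Adjusting for a complete, prognostic baseline variable usually raises power without raising the type I error. It also guards against chance imbalance in baseline severity, which neither the randomisation nor the stated analyses address for PI. The sample size is set at 80% power for the evaluable number, so there is little reserve beyond the dropout allowance.

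**Working it through.** **1. Reproduce the plan's sample size.** Inputs from Proposed sample size/power calculations: placebo rates 0.42 (low risk) and 0.69 (high risk), a 2:1 low-to-high ratio, odds ratio 0.5, two-sided alpha 0.05, power 80%. Allocation of 1:1 is assumed, since the article gives no ratio.

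- PETN rate in each stratum: q = 0.5p / (1 − p + 0.5p), giving 0.2658 and 0.5267.
- Weights w are 2/3 and 1/3; m is the mean of p and q in a stratum (0.3429 and 0.6084).
- A = Σ w·m(1−m)/4 = (2/3 × 0.2253 + 1/3 × 0.2383)/4 = 0.0574
- B = Σ w·[p(1−p) + q(1−q)]/8 = (2/3 × 0.4388 + 1/3 × 0.4632)/8 = 0.0559
- D = Σ w·(p−q)/4 = (2/3 × 0.1542 + 1/3 × 0.1633)/4 = 0.0393
- N = (1.960·√A + 0.842·√B)² / D² = 289.3, rounded up to **290**, as stated. Power at 290 is **80.1%**.
- 290/0.9 rounds up to 323, against the stated 324, which is within rounding.

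Pooling the strata would need 310 women, so stratifying by risk group already removes about 6% of the outcome variance.

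**2. What PI could add, from the protocol's own accuracy figures.** The gradient above 1.6 is not given. As an assumption, take PI as normal with equal variance in women with and without FGR. The log-odds slope, per SD of PI in women without FGR, is then d = z(specificity) + z(sensitivity):

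- general population: 1.645 − 0.915 = 0.729
- high-risk population: 0.674 + 0.202 = 0.876

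Enrolment keeps only women above the cut-off, which shrinks the spread of PI. The SD after truncation is 0.414 (low-risk stratum, general-population figures) and 0.612 (high-risk stratum, high-risk figures). The odds ratio per in-trial SD is therefore exp(0.729 × 0.414) = 1.35 to exp(0.876 × 0.612) = 1.71, that is, log-odds of about 0.30 to 0.54.

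Let R² be the share of within-stratum outcome variance explained by PI. The required N scales as 290 × (1 − R²). Power at N = 290 is Φ(D·√(290/[A(1−R²)]) − 1.960). This simpler formula gives 79.8% without PI, and gains are measured from that figure.

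| Accuracy figures used | R² | N for 80% power | Power at 290 |
|---|---|---|---|
| None (no PI) | 0 | 290 | 79.8% |
| General population in both strata | 0.020 | 284 | 80.6% |
| General in low risk, high-risk in high risk | 0.031 | 281 | 81.0% |
| High-risk in both strata | 0.054 | 274 | 81.9% |

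The gain is 0.8 to 2.1 points, or 290 − 284 = 6 to 290 − 274 = 16 evaluable women.

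**3. Wider assumed range.** Simulated trials with N = 290 and the planning rates compared the Mantel-Haenszel test with a logistic score test adjusted for risk group and PI. At log-odds per SD of 0, 0.3, 0.5 and 0.8 the gains were about 0, 0.6, 2.2 and 4.2 points. A separate run of 6,000 trials per setting gave 0.5, 2.0 and 4.3 points at 0.3, 0.5 and 0.8, with type I error of the adjusted test at 4.6% to 5.4%. There was no meaningful loss when PI carried no information.

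**4. Scale in recruitment terms.** The Recruitment section expects about 13,000 scanned women for 324 randomised, or about 40 each. After 10% dropout, 6 to 16 evaluable women correspond to 6/0.9 × 40 ≈ 270 to 16/0.9 × 40 ≈ 710 scans.

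**The case against.** The strongest reply is that nothing here is wrong. Randomisation is stratified by risk group, the sample size is calculated for a Mantel-Haenszel test over those strata, and that same test is the confirmatory one. It is valid and delivers the power claimed. This stands in full.

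The statement that impaired flow is strongly associated with FGR, and the accuracy figures beside it, concern a yes/no cut-off that every enrolled woman has already passed. Much of PI's information may be spent on selection, and no section says that PI predicts outcome above 1.6. This also stands, and it is why the gain may be zero.

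A reader might infer from the protocol's wording that substantial power is being given away, say 3 to 4 points. The documents do not support that. Such a gain needs log-odds of nearly 0.8 per SD, steeper than the 0.30 to 0.54 derived from the protocol's own figures. Nor is the change entirely free: a Mantel-Haenszel test cannot take a continuous covariate, so the confirmatory method would change and a functional form for PI would have to be chosen.

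Omitting PI from the mixed model is not a defect, since that model is there for centre effects. A separate analysis plan may add a supportive PI-adjusted analysis. It could not make PI part of the confirmatory test without departing from the article, which names that test.

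The worry that a conditional odds ratio changes the quantity estimated is met by reporting a standardised relative risk.

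**Conclusion.** The point holds as an optional efficiency improvement. Baseline PI is available before treatment in every randomised woman, the protocol treats it as a marker of FGR risk, and no stated analysis uses its value. The planned test is neither invalid nor underpowered on its own inputs.

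The best estimate that the documents allow is a gain of about 1 to 2 power points. It rests on the cited accuracy figures carrying over to this population, an equal-variance binormal model, truncation at the cut-off and 1:1 allocation. Protection against chance imbalance in PI is a further, unquantified benefit.

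**What to change.** Before unblinding, amend the Statistical analysis section as follows:

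- Make the confirmatory test a logistic score test for treatment, adjusted for risk group and for log mean uterine artery PI at inclusion as a continuous covariate.
- Report a standardised (marginal) relative risk with its 95% confidence interval, so that the relative-risk scale is kept.
- Keep the unadjusted risk-stratified Mantel-Haenszel test and relative risk as the supportive analysis.

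The cost is one amendment of the analysis wording and a functional form for PI that is fixed in advance. No new data and no extra patients are needed. The sample size should stay as planned, because the gain rests on an unverified gradient. If the sponsor prefers to leave the confirmatory test unchanged, the existing plan remains sound.
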